#### Clinic Recruitment and Consent Process

Primary care clinics will be identified according to the geographical area in which many US Vietnamese patients receive health care services. Prior to recruiting clinics of large health care systems, permission will be sought from the responsible administrators and medical directors. Independent and privately owned clinics will receive an invitation letter describing this study and its aims. Clinics that respond to the invitation will be assessed for eligibility by the principal investigator (PI). Clinics that do not respond to the initial mailed letter within 2 weeks will be contacted by email or phone.

Once the clinics are determined to be eligible, the PI will contact the office manager and the health care provider to ask for approval for the clinics to participate and obtain consent from these individuals. Next, the PI will set up 2 sessions of 1 hour briefing about this study and 1 hour training with clinic staff. Then participating clinics will identify and refer interested patients with a diagnosis of T2D via telephone contact or email.

#### Patient Recruitment and Consent Process

This study will recruit 80 patients from 10 clinics, approximately 8 patients from each clinic. We expect to have approximately 5 to 6 patients complete this study from each clinic giving a 70% (n=56) study completion rate. The power calculation was conducted by using the linear mixed effect modeling of the R (R Foundation for Statistical Computing) package “*swdpwr*,” which gives power of 0.95 for the alternative hypothesis treatment effect change of 0.005 (2-sided type I error 0.05). The recruitment strategy includes a letter and flyer to be sent by the clinics with the research team’s contact information. Study information will be provided to those who reach out to a research team member with their interest and an opt-out contact will be applied after 3 days of receiving the letter. A member of the research team will arrange a time to meet with eligible patients to discuss the option to participate in this study, complete the informed consent procedure, complete this study’s screener, and enroll them in this study if the individual is both eligible and interested. All patients will have the option of completing the consent and confidentiality forms in English or Vietnamese language. Upon full study enrollment, a member of the research team will collect baseline data.

#### Randomization

Because individual randomization is not feasible due to potential contamination of the intervention for control participants, this study will use a programmatic roll-out in a stepwise fashion where each clinic that is not yet receiving the intervention will function as a control. Another reason for the selection of a stepped wedge design is that the measurement of outcomes is at the clinic level and individual patient level. Randomization of the intervention sequence will be conducted at the level of the clinics with computer-generated assignment using SAS (version 9.4; SAS Institute) by a statistician blinded to the identity of the clinics and not involved in the intervention delivery. The clinics will be randomized from 1 through 10 and will be allocated a date of implementation which will be concealed until interventions are assigned. Clinics will be informed that the order of allocation to the intervention will be unknown in advance of randomization.

During the initial control period, no clinic will be exposed to the intervention. Subsequently, at each 3-month interval, 1 clinic will transition from the control to the intervention period. This staggered schedule will allow for optimal training, implementation, and supervision of clinic staff. The process will continue until all 10 clinics have crossed over to receive the intervention. Figure 1 illustrates this study’s procedures.

**Figure 1 figure1:**
[figure not shown]
Study procedures for a randomized clinical trial in collaboration with primary care clinics. SDSCA: summary of diabetes self-care activities.

#### Data Collection

At enrollment, participants will complete the self-report demographic information survey, which will include age, gender, years of residence in the United States, and clinical information about their current treatment regimen to characterize the sample. For baseline data, participants will also complete the validated Summary of Diabetes Self-Care Activities (SDSCA) scale to measure self-care behaviors. The SDSCA scale, available in both English and Vietnamese languages, measures the participant’s management of diabetes in the last 7 days regarding diet, physical activity and exercise, blood glucose testing, foot care, and smoking. Participants answer 11 questions by indicating the number of days the behavior was followed in the past 7 days (0-7 days). In addition to self-reported behaviors, lab test results including triglyceride, low-density lipoprotein, high-density lipoprotein, hemoglobin A_1c_, and clinical assessments including BMI, blood pressure, and weight will be collected from their medical chart and entered into Research Electronic Data Capture (Vanderbilt University), a secure database. This information will be collected again at completion of the 12-week program and at 6 months, 9 months, and 12 months from baseline. Table 1 describes the timing of data collection and evaluation plan by the RE-AIM framework.

**Table 1 table1:** Data collection and evaluation plan using RE-AIM^a^ framework: assessment objectives, data, instruments, and timeline.

RE-AIM domain		Method	Baseline	Follow-ups (months after baseline)			
				3	6	9	12
Demographic patient information		Paper questionnaire	✓	N/A^b^	N/A	N/A	N/A
Clinic or facility information		Paper questionnaire	✓	N/A	N/A	N/A	N/A
**Reach: absolute number and characteristics of those participating in the intervention**							
	Percentage of eligible patients who respond to texts and nurse calls at least 1 week of program	mHealth^c^ data and field notes	✓	N/A	N/A	N/A	N/A
	Differential characteristics between participating and nonparticipating patients	Clinic data and field notes	✓	N/A	N/A	N/A	N/A
	Barriers and facilitators to reach	Focus groups or interviews	✓	N/A	N/A	N/A	N/A
**Effectiveness: modification in self-care behavior and improvement in biological markers**							
	Changes in SDSCA^d^ scale	Paper questionnaire	✓	✓	✓	✓	✓
	Changes in triglyceride, LDL^e^, HDL^f^, HbA_1c_^g^, BMI, BP^h^, weight	Clinical assessment and lab results	✓	✓	✓	✓	✓
	Percentage of patients enrolled at end of study period	Enrollment data	✓	✓	✓	✓	✓
**Adoption: intervention adoption at clinic and patient level**							
	Percentage of eligible clinic sites who participated	Enrollment data	✓	N/A	N/A	N/A	N/A
	Barriers and facilitators to adoption	Focus groups or interviews	✓	N/A	N/A	N/A	N/A
**Implementation: key features of program delivery**							
	Fidelity to the protocol	mHealth data and field notes	✓	✓	✓	✓	✓
	Barriers and facilitators to implementation (feasibility and acceptability)	Focus groups or interviews	✓	✓	N/A	N/A	N/A
**Maintenance: extent of clinics sustaining the program and patients maintaining improved outcomes**							
	Sustainability of intervention at each site through end of study period	Focus groups or interviews	✓	✓	✓	✓	✓
	Sustainability of improved outcomes through the end of the study period	Clinical assessments and lab results	✓	✓	✓	✓	✓

^a^RE-AIM: Reach, Effectiveness, Adoption, Implementation, Maintenance.

^b^N/A: not applicable.

^c^mHealth: mobile health.

^d^SDSCA: summary of diabetes self-care activities.

^e^LDL: low-density lipoprotein.

^f^HDL: high-density lipoprotein.

^g^HbA_1c_: glycated hemoglobin.

^h^BP: blood pressure.

#### Outcome Measures

The primary outcomes are the degree of reach, effectiveness, adoption, implementation, and maintenance measured by using the RE-AIM framework [31]. Reach is the ability to recruit patients and will be determined by assessing the number of people who received an invitation over the number of those who may be eligible to participate in the same clinic. Data sources include the number of invitations and the number of eligible patients seeking care at the clinic. Adoption will be measured by the proportion of clinicians who used the program and the number of patients who participate in the intervention by assessing the number of enrolled participants over the number of those invited, 3 months after the initiation of the intervention. Program implementation will be assessed by conducting a focus group or interview with the clinicians and patients separately at each clinic to gather feedback. Differences and similarities will be compared within and across clinics to identify emerging themes. Barriers and facilitators to program adoption by clinics will also be identified. See Table 2 for postintervention focus group or interview questions.

**Table 2 table2:** Postintervention focus group or interview questions for participants.

Measures	Interview questions
Acceptability	How would you describe your experience of taking part in this tailored DSMES^a^ program? What aspect of the program did you like the most? What was your favorite session? Suppose a friend of yours was diagnosed with diabetes and came to you for advice. What would you tell them about this DSMES program?
Process of change	What did you learn from this program? How has your perspective of living with diabetes changed since completing the program? What differences have you noticed in your life as a result of taking part in this DSMES program?
Barriers	What kind of difficulties did you experience taking part in this DSMES program?
Improvement	What did you least like about the program? What do you think could be improved about this DSMES program?
Implementing change	How often do you practice the self-care behaviors such as following a healthy eating plan, testing your blood sugar, caring for your foot, etc. learned from this program?

^a^DSMES: diabetes self-management education and support.

The secondary outcomes are self-reported changes in behaviors and clinical test results, which will be compared to determine intervention maintenance and effectiveness. Repeated outcome measures will be assessed at 5 points in time. The translated and validated SDSCA revised scale [32] will be used to measure behavioral changes and assess 5 topics: diet, physical activity and exercise, blood glucose testing, foot care, and smoking. The average interitem correlations within scales were high (mean *r*=0.47) with the exception of specific diet; test-retest correlations were moderate (mean *r*=0.40). Correlations with other measures of diet and exercise generally supported the validity of the SDSCA subscales (mean *r*=0.23). Triglyceride, low-density lipoprotein, high-density lipoprotein, hemoglobin A_1c_, BMI, weight, and blood pressure will be used to measure clinical changes, which will be obtained from the participants’ medical records. Participants will be monitored for an additional 9 months via chart reviews and self-report using the SDSCA scale to determine whether any improvements observed at completion of the intervention will still be evident.

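### Reach, a primary outcome, is computed in the text as invited over eligible, with no participation term, while Table 1 measures it by patients' response to the programme

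*Protocol article*

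**What the plan says.** All statements are in the protocol article.

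- **Status.** Outcome Measures: "The primary outcomes are the degree of reach, effectiveness, adoption, implementation, and maintenance measured by using the RE-AIM framework".
- **Concept in the text.** The same paragraph: "Reach is the ability to recruit patients".
- **Formula in the text.** Reach "will be determined by assessing the number of people who received an invitation over the number of those who may be eligible to participate", taken clinic by clinic.
- **Data sources in the text.** "Data sources include the number of invitations and the number of eligible patients seeking care at the clinic". No enrolment count is listed.
- **Table 1, Reach heading.** "Reach: absolute number and characteristics of those participating in the intervention".
- **Table 1, Reach percentage.** "Percentage of eligible patients who respond to texts and nurse calls at least 1 week of program", taken from mobile-health platform data and field notes.
- **Adoption.** Outcome Measures includes enrolled over invited patients, three months after the intervention starts. Table 1's only quantitative Adoption row is "Percentage of eligible clinic sites who participated", although the heading above it covers both clinics and patients.
- **Participation elsewhere.** Hypothesis 1 expects at least 50% of invited eligible patients to take part. Data Analysis lists the share of eligible people who agree to take part as a descriptive feasibility statistic.

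**The concern.** The formula does not measure the concept stated in the same sentence. Ability to recruit depends on how many patients join, but invited over eligible counts only the offers made. It also disagrees with Table 1, which ties Reach to people in the programme and draws on a different data source.

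The Abstract says the study is meant to inform later scale-up. Anyone reading a Reach percentage for that purpose will take it as the share of eligible patients the programme got to. Computed as the text directs, the figure does not respond to uptake at all. Computed as Table 1 directs, it answers a different question, about engagement. With both in print, a reader of the results cannot tell which one the label Reach refers to.

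**Working it through.** The article gives no value or target for Reach, so there is no plan figure to reproduce. The check compares the ratios.

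**Notation, per clinic or pooled.** N = eligible patients, I = invited, P = enrolled, W = patients meeting Table 1's response criterion.

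| Quantity | Where | Formula |
|---|---|---|
| Reach, text | Outcome Measures | I / N |
| Reach, table | Table 1 | W / N |
| Patient part of Adoption (uptake) | Outcome Measures | P / I |
| Enrolled share of eligible patients | product of rows 1 and 3 | (I / N) × (P / I) = P / N |

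**Step 1: behaviour of the text's formula.** Neither P nor W appears in I / N. If I = N, the ratio is 100% for every value of P, including P = 0. This needs no assumed count.

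**Step 2: ordering.** If everyone who enrols was invited, and only enrolled patients receive messages and calls, then W ≤ P ≤ I ≤ N. Hence W / N ≤ P / N ≤ I / N, and the text's version is always the largest of the three.

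**Step 3: size of the gap.** (I / N) ÷ (P / N) = I / P = 1 ÷ uptake. The result does not depend on N.

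- Uptake 25%: 1 / 0.25 = 4 times the enrolled share.
- Uptake 50%, the hypothesis 1 threshold: 1 / 0.50 = 2 times.
- Uptake 100%: 1 / 1.00 = 1, no difference.

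**Step 4: illustration.** The article gives neither N nor W. N = 160 and all values of W are assumptions. An enrolment of 80 is the recruitment target, and 40 is the number attached to the 50% in hypothesis 1.

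| N | I | P | W | Text Reach I/N | P/N | Table 1 Reach W/N |
|---|---|---|---|---|---|---|
| 160 | 160 | 0 | 0 | 100% | 0% | 0% |
| 160 | 160 | 40 | 30 | 100% | 25% | 18.75% |
| 160 | 160 | 80 | 56 | 100% | 50% | 35% |
| 160 | 80 | 80 | 56 | 50% | 50% | 35% |
| 160 | 80 | 40 | 30 | 50% | 25% | 18.75% |

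In rows 1 to 3 uptake changes and the text's Reach stays at 100%. Between rows 3 and 4 only the number of invitations changes: the text's Reach falls from 100% to 50% while the enrolled share stays at 50%. The W / N column follows from the assumed W and carries no weight beyond showing that it is a third, different number.

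**The case against.** **Participation is captured anyway.** This is the strongest reply, and it stands. Enrolled over invited is defined in the same paragraph, and multiplying it by invited over eligible recovers enrolled over eligible. With no enrolment, the adjacent uptake figure would read 0%. A reader might infer that the study cannot say how many patients joined; the article does not support that. The zero-uptake row is also only a property of the formula, since the Results section reports 60 patients already enrolled.

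**Reach drives no decision.** Also correct. No threshold, test or progression rule is attached to Reach, and hypothesis 1 is framed on invited patients, so either definition leaves it unchanged. A reader might infer that the conflict lets the trial's conclusion be chosen after the data are seen. The documents support only the narrower point that it is open which descriptive percentage is called Reach.

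**Adoption.** A reader might see a second contradiction here, because the text includes enrolled over invited while Table 1 counts clinic sites. Table 1's Adoption heading names the patient level as well, so the two are compatible. The table merely lacks a row for a measure its heading covers.

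**Invited over eligible has some use.** It does. The clinics send the letters, so the ratio shows how fully clinics extend the offer. It should not be dismissed as a number fixed by the study team. That is a reason to report it under its own name, not to call it Reach.

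**A slip, or journal condensation.** One could read the formula as meaning people who accepted an invitation. The listed data sources, invitation and eligibility counts only, do not support that reading. Nor is this detail left to a fuller document: two explicit definitions are printed and they disagree.

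**Conclusion.** The point holds as a defect in the definition of one descriptive primary outcome. The text's formula omits participation, does not match its own stated concept, and conflicts with Table 1 in numerator and data source. The text's Reach exceeds the enrolled share of eligible patients by a factor of 1 / uptake: two at the 50% uptake of hypothesis 1, and none if everyone invited enrols.

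This assumes that the eligible denominator is the same group in the text and in Table 1, and that enrolled patients are counted among the invited. The 100% result under full invitation needs neither assumption.

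The consequence is a mislabelled and ambiguous Reach figure. It is not missing data, and it does not affect the test of hypothesis 1. It is worth correcting because Reach is named as primary and the study is meant to inform scale-up.

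**What to change.** 1. Use one definition in both Outcome Measures and Table 1: Reach = enrolled patients / eligible patients at participating clinics. Add the enrolment count to the data sources listed for Reach.
2. Report invited / eligible separately, labelled invitation coverage.
3. Keep enrolled / invited as the uptake measure for hypothesis 1. It may stay under patient-level Adoption; Table 1 should then carry a row for it.
4. Keep the measure of response to messages and coaching calls, with its criterion of at least one week unchanged, as a separately labelled engagement measure.

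**Cost.** Text edits to one paragraph and the affected rows of Table 1. Eligible, invited and enrolled counts and platform response data are already planned, so design, sample size and data collection do not change. The reported Reach figure may be lower than under the text's present formula.

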#### Data Analysis

To evaluate the first hypothesis, descriptive statistics will be used to analyze the acceptability and feasibility of the intervention, which include the proportion of individuals who met the criteria, proportion of eligible participants who agreed to participate, the proportion of mHealth responses completed, and attrition rate at follow-up periods. A linear regression model will be used to examine the association of response rate and attrition rate with other predictors. To evaluate the second hypothesis, continuous variables will be calculated using descriptive statistics including quantiles, mean, and SD. To examine the association of continuous outcome variables and other predictors, a linear mixed effect model will be used to examine time effects, clustering effects, and the interaction of the two. Transformation of outcome variables will be conducted to normalize the nonnormal distributions. To examine the association of categorical outcome variables and other predictors, a generalized linear mixed effect model will be used to examine time effects, clustering effects, and the interaction of the two. In order to handle missing values, sequential multiple imputation will be performed before the analysis. SAS (version 9.4; SAS Institute) will be used for statistical analysis.

To analyze qualitative data from the focus groups and interviews, field notes will be transcribed for coding and analysis. Focus groups and interviews conducted in Vietnamese will be translated into English by the research assistant and verified by the PI before coding and analyzing thematically. Prior to analyzing the transcripts, the researchers will read the transcripts at least twice and compare them with the field notes to ensure accuracy and completeness. Selected transcripts will be reviewed by an experienced qualitative researcher to compare the consistency in developing a coding schema. The NVivo (Lumivero) software will be used to manage and analyze qualitative data.

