## Discussion

This study is driven by two hypotheses: (1) at least 50% (n=5) of eligible clinics and 50% (n=40) of eligible patients who are invited will participate, and at least 70% (n=56) of patients will complete the program, and (2) patients who receive the intervention will have improved self-care behaviors and improved clinical test results with at least 75% (n=60) of the patients maintaining improved outcomes at follow-up visits compared with baseline, and participants will verbalize that the intervention is feasible and acceptable. This protocol was designed with an interprofessional research group that has many strengths. An overall strength is the stepped wedge design, which allows participating clinics to be randomized with an opportunity for all consented patients to participate in the intervention. The staggering of clinic implementation allows the research team to train clinic staff and monitor potential implementation issues. The mixed method and longitudinal design provide insights into long-term outcomes over time.

Another strength of this protocol is this is the first Vietnamese DSMES intervention to be implemented in collaboration with primary care clinics that leverages mHealth technology to address the barriers of language and cultural differences. Vietnamese-speaking individuals have few opportunities to participate in health-related randomized clinical trials. This protocol allows that opportunity because it is offered in the Vietnamese language to promote self-determination and independence, and improve self-management strategies.

Further, 1 limitation of the stepped wedge design is that patients of clinics that were randomized for implementation later will have to wait months before receiving the intervention. This waiting period may reduce engagement with the researchers and may increase attrition rates. Another limitation is the repeated measurements of questionnaires and clinical tests may lead to a higher respondent burden on patients and clinic staff.

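### Response and attrition rates are to be analysed by linear regression with no clinic term and no stated unit; if patients are the unit, standard errors for mainly between-clinic predictors are too small

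*Protocol article*

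**What the plan says.** The Data Analysis section (protocol article, Methods) assigns models by type of outcome.

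- **Feasibility and acceptability (hypothesis 1).** Descriptive statistics come first. They include "the proportion of mHealth responses completed, and attrition rate at follow-up periods". The modelling sentence then follows: "A linear regression model will be used to examine the association of response rate and attrition rate with other predictors". It mentions neither clinic nor clustering and does not say whether a data point is a patient, a visit or a clinic.
- **Continuous outcomes (hypothesis 2).** Here "a linear mixed effect model will be used to examine time effects, clustering effects, and the interaction of the two".
- **Categorical outcomes (hypothesis 2).** "To examine the association of categorical outcome variables and other predictors, a generalized linear mixed effect model will be used", with the same time and clustering terms.

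On size, Patient Recruitment and Consent Process states: "This study will recruit 80 patients from 10 clinics, approximately 8 patients from each clinic". It continues: "We expect to have approximately 5 to 6 patients complete this study from each clinic giving a 70% (n=56) study completion rate". The Randomization section makes the clinic the unit of randomisation, with one clinic crossing over every 3 months. The Discussion says of clinics allocated a late start: "This waiting period may reduce engagement with the researchers and may increase attrition rates".

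**The concern.** Patients of one clinic share staff, referral practice and a randomised start date, so their drop-out and message response are likely to be correlated. The plan accepts this for the behavioural and clinical outcomes but not for response and attrition. The linear model is a named choice, so this is more than a detail left to an analysis plan.

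Two consequences follow if the regression is run on patients. First, a straight-line model is fitted to a yes/no outcome (attrition) and to a proportion confined to 0 to 1 (response), and fitted attrition can fall outside that range. Second, a predictor that is constant within clinic is tested as if there were 80 independent values when there are 10. The randomised step is the clearest example, and it largely drives the waiting time that the Discussion links to attrition.

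At stake is what the pilot says about who drops out or stops responding, which would inform the intended scale-up.

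**Working it through.** **Inputs from the protocol article.** 10 clinics, about 8 patients each, 70% expected completion (Patient Recruitment and Consent Process).

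**The plan's own figures.** 10 × 8 = 80; 0.70 × 80 = 56; 56 / 10 = 5.6 completers per clinic. These reproduce the stated 56 and 5 to 6. Expected drop-outs are 80 − 56 = 24.

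**Assumption.** No ICC for attrition or response is given, so a range is shown.

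**Patient as unit, predictor constant within clinic.**

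- Variance inflation ignored by the plain regression: D = 1 + (8 − 1) × ICC.
- Factor by which the standard error is too small: √D.
- Actual level of a nominal 5% two-sided test: 2 × [1 − Φ(1.96 / √D)].

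The formula was checked by simulation: 20,000 runs, 10 clinics of 8, 30% attrition, beta-binomial clustering, equally spaced steps and no true effect of step.

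| Assumed ICC | D | √D | Level, formula | Level, simulated | True SE / mean reported SE, simulated |
|---|---|---|---|---|---|
| 0.01 | 1.07 | 1.03 | 5.8% | 6.0% | 1.04 |
| 0.05 | 1.35 | 1.16 | 9.2% | 9.3% | 1.17 |
| 0.10 | 1.70 | 1.30 | 13.3% | 13.5% | 1.32 |
| 0.20 | 2.40 | 1.55 | 20.6% | 20.8% | 1.58 |

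With ICC 0 the simulated level was 4.9%. If only the 5.6 completers per clinic entered a model, √D would be 1.02, 1.11 and 1.21 at ICC 0.01, 0.05 and 0.10.

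**Patient as unit, predictor varying within clinic.** The inflation becomes approximately 1 + 7 × ICC × ICCx, where ICCx is the predictor's own intracluster correlation. At ICC 0.10:

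- ICCx = 0.1 (assumed, mainly within clinic): 1 + 7 × 0.10 × 0.1 = 1.07, factor 1.03.
- ICCx = 0.5 (assumed, mixed): 1 + 7 × 0.10 × 0.5 = 1.35, factor 1.16.

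The full factor applies only when ICCx = 1.

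**Clinic as unit.** Regressing the 10 clinic proportions on step gave a simulated level of 4.8% to 5.1% at every ICC tried, so the standard error is not understated. With 10 − 2 = 8 degrees of freedom the critical t is 2.306. A correlation must therefore exceed 2.306 / √(2.306² + 8) = 0.63 to reach p < 0.05, and patient-level predictors can enter only as clinic averages.

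**The case against.** The strongest reply is that the article never says the regression is on patients. It speaks of rates, and a rate can belong to a clinic or a visit; on clinic rates the error level is correct. This stands, so the finding has to be conditional on the unit. The patient reading is still the more natural one: Table 1 defines response and retention by counting patients, and the sentence speaks of several predictors, which 10 points could hardly support.

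A reader might infer that waiting time is a planned predictor and varies only between clinics, so that the full factor applies to it. The article supports neither. The model sentence names no predictor, and waiting time appears only as a limitation in the Discussion. The crossover date is fixed by clinic, but a patient's wait also depends on the enrolment date. Recruitment began on November 4, 2022, and 60 patients were enrolled by August 24, 2023, so waits may differ within a clinic. The full factor belongs to the randomised step; for waiting time it is an upper limit.

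A reader might also infer that the verdict on hypothesis 1 is at risk. It is not. The 50% and 70% criteria are observed proportions, evaluated descriptively.

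It is also fair to say that with at least one message a day for 12 weeks (84 or more per patient), a linear model for the response proportion is a workable approximation, and that degrees of freedom and covariate lists can be left to an analysis plan. That softens the point about model form for response. It does not answer the missing clinic term, nor the linear model for binary attrition.

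**Conclusion.** The point holds in conditional form. The plan fixes a linear regression without clinic for two clustered feasibility measures and does not state the unit of analysis.

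With patients as the unit, the model form does not suit binary attrition, and inference on mainly between-clinic predictors is too optimistic. The distortion is negligible at the low end of the assumed ICC range and material at the high end; nothing in the article says which end applies. With clinics as the unit, the inference is valid but very imprecise. The sentence needs repair under either reading.

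The consequence is confined to exploratory associations. Neither the hypothesis 1 thresholds nor the models for behavioural and clinical outcomes are affected. It should be corrected because the remedy is already in the same paragraph.

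**What to change.** Replace the sentence so that it does the following:

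1. Names the patient as the unit of analysis.
2. Uses the generalized linear mixed model already planned for categorical outcomes: logistic for attrition, and binomial (responses out of messages requiring one) with an overdispersion term for message response.
3. Includes a random clinic intercept and small-sample degrees of freedom suited to 10 clinics.
4. Names in advance only a few predictors, since about 24 drop-outs are expected. If the effect of waiting is of interest, it should say whether that means the clinic's randomised step or the patient's own time from enrolment to crossover.

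**Cost.** One sentence, the same software and no new data. Intervals for clinic-level predictors widen: standard errors grow by about 3% to 30% over ICC 0.01 to 0.10. If degrees of freedom fall from 78 to 8, the critical t also rises from 1.99 to 2.31, a ratio of 1.16. Together, interval width grows by about 1.03 × 1.16 = 1.20 to 1.30 × 1.16 = 1.51 times. That is the precision 10 clinics can give. Predictors that vary mainly within clinic lose little.
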